## Abstract

**Background:**

Puberty in girls is occurring earlier worldwide with a declining trend over the recent decades, resulting in increased attention on the accompanying risks of psychosocial challenges and adverse health outcomes for the affected girls. Diverse mechanisms have been proposed as mediators of the tendency for earlier pubertal maturation, including a shift toward a more sedentary lifestyle and changes in dietary habits leading to childhood obesity. Several studies have demonstrated a potential association between the rise in childhood obesity prevalence and the decline in the age at which puberty begins. Increased insulin resistance is thought to play a role in this connection, and previous studies indicated that improved insulin sensitivity following either treatment with metformin or weight loss could delay pubertal progression in girls with overweight.

**Methods:**

LIFE-MET is a randomized, placebo-controlled, four-arm, multicenter trial of girls (*n* = 80) with overweight and early puberty. Allocation to metformin or placebo will be double-blinded. Eligible girls will be randomly assigned to one of the four study arms: Metformin + lifestyle intervention (*N* = 20), Metformin alone (*N* = 20), Placebo + lifestyle intervention (*N* = 20), Placebo alone (*N* = 20). The intervention period is 6 months with a follow-up after an additional 6 months. The primary outcome is the change in bone age from baseline to 12 months, as a marker of pubertal progression. Secondary outcomes include changes in body composition, Tanner stage, fitness level, sex hormones, insulin resistance, and age at menarche.

**Discussion:**

New strategies not only for the treatment but also for the prevention of both overweight and early puberty are needed. The LIFE-MET trial is a randomized controlled trial with a combination of lifestyle intervention including online, virtual reality training and a pharmacological intervention consisting of metformin and/or placebo, to our knowledge the first of its kind. We expect that this intervention will have a beneficial effect on both pubertal progression, daily physical activity level, and body composition. Additionally, a healthier body composition may have beneficial effects on long-term co-morbidities related to early puberty.

**Trial registration:**

Clinical Trial Information System (CTIS): 2024-511009-50-00. Approved 04/30/2024. https://euclinicaltrials.eu/search-for-clinical-trials/?lang=en&EUCT=2024-511009-50-00.

## Administrative information

NOTE: the numbers in curly brackets refer to SPIRIT checklist item numbers [1]. The order of the items has been modified to group similar items (see http://www.equator-network.org/reporting-guidelines/spirit-2013-statement-defining-standard-protocol-items-for-clinical-trials/).

Composition, roles, and re-sponsibilities of the coordina-ting centre, …, and other individuals or groups overseeing the trial {5d}	The coordinating centre (Department of Pediatrics and Adolescent Medicine, Herlev and Gentofte Hospital) is composed by PI and trial sponsor [name] and daily coordinating investigator GL. The local nurses and PI’s at each center will provide day-to-day support for the trial. Regular meetings between PI’s will take place to coordinate and supervise the tasks. The trial will be monitored by the Good Clinical Practice (GCP) Units. See {21a} for data monitoring committee.

## Introduction

### Background and rationale {6a}

Puberty in girls is occurring earlier worldwide with a descending trend over the recent decades [2–8]. The age of breast development has declined most markedly [3, 5, 6] but several studies have also demonstrated an earlier age at menarche, although to a lesser extent [6, 9–13]. The onset of puberty is strongly influenced by genetic factors; however, genetics cannot account for the significant changes observed in the changes in age at pubertal onset. Diverse mechanisms have been proposed as mediators of earlier pubertal maturation. These include improvements in health and nutrition [14, 15], as well as lifestyle factors such as sedentary behavior and dietary practices that contribute to childhood obesity [2]. Early puberty is associated with several adverse health outcomes, but short-term consequences are primarily adverse mental health outcomes such as depression, anxiety, and eating disorders, as well as increased risk-taking behavior and earlier onset of sexual activity [16–18]. Long-term health challenges include an increased risk of type 2 diabetes, cardiovascular disease, and breast cancer [16, 19–22]. Taken together, this necessitates continued attention on understanding the underlying mechanisms affecting the initiation of puberty.

### Increasing incidence of childhood overweight and relation to early puberty

For several decades, the prevalence of childhood obesity has escalated globally and remains high [23–26]. According to the World Health Organization, 29% of European children aged 7–9 years were overweight during the period 2018–2020 [26].

Recent epidemiological studies have demonstrated a potential association between the rise in obesity prevalence and the decline in the age at which breast development begins [27, 28]. However, this relationship does not confirm obesity as a causal factor of earlier puberty, and this remains a subject of debate. Several mechanisms have been proposed, including increased insulin resistance [29].

Children with obesity often exhibit increased levels of androgens from both the adrenal glands and ovaries, as a response to the increased insulin resistance and compensatory hyperinsulinemia [24, 30]. Insulin resistance is also associated with decreased concentrations of sex hormone binding globulin (SHBG), resulting in an increased availability of sex steroids [29]. Evidence suggests that not only adiposity but also the “mismatch” between low birth weight and rapid weight gain in early infancy may influence pubertal timing, likely due to increased production of adrenal androgens and decreased insulin sensitivity [24, 30–32].

Normal puberty is a period characterized by insulin resistance [33, 34], and a recent systematic review and meta-analysis demonstrated an independent association between early age at menarche and insulin resistance, also when adjusting for total body fat percentage [35–37]. The causal relationship is still uncertain, but supporting the role of insulin resistance in early menarche are the clinical studies of Ibañez et al. Focusing on girls born small for gestational age (SGA) experiencing early puberty, they revealed that treatment with metformin, which enhances insulin sensitivity, delayed pubertal progression and age at menarche by nearly 1 year compared to the untreated group [38]. In another study of girls with low birth weight and precocious pubarche, metformin lowered androgen levels and delayed the clinical onset of puberty by 0.4 year [39]. Additionally, a clinical study of children with overweight participating in a 1-year weight loss program including lifestyle interventions demonstrated that weight loss was associated with a significant later onset of puberty in girls [40]. Thus, there is some evidence that improved insulin sensitivity obtained either by treatment with metformin or following weight loss could delay pubertal progression in girls.

### Physical activity and timing of puberty

Increased levels of physical activity have been linked to later pubertal maturation, the most pronounced association being for professional athletes [41, 42]. A randomized controlled trial (RCT) examining the impact of combined lifestyle changes (diet, decreased television viewing, and PA) on the timing of puberty demonstrated a 25% lower relative risk of reaching menarche during the study period for the girls in the intervention schools compared to control schools [42]. The effects of increased PA on the progression of puberty have been proposed to be mediated by changes in body composition, in particular adipose tissue and thereby leptin secretion [43], and improved insulin sensitivity. Overall, the evidence of an association between PA and age at menarche remains sparse, as most former studies were historical cohorts or case-control studies [41].

Searching for innovative methods to make children and adolescents more physically active, the effect of exergames or active video games (AVGs) on PA level and BMI reduction has been examined in several RCT studies [44–49]. Trost et al. [50] found that incorporation of AVGs into a pediatric weight management program had positive effects on physical activity and relative weight. Another study concluded that exergaming at home lowered BMI z-score and physical activity levels in children aged 10–12 years with overweight or obesity and proposed that exergaming with social support could be promoted as an exercise option for children [44]. Accordingly, AVGs could be considered a possible supplement in the management of overweight and sedentary lifestyle in children and adolescents.

### Perspectives and aim of this trial

The overall aim of this trial is to explore whether a novel alternative treatment strategy for girls with overweight and early puberty can postpone pubertal maturation. Our hypothesis is that lifestyle factors and adiposity influence pubertal onset and that this process may be reversible through improvement of insulin sensitivity and/or weight loss or changes in body composition.

### Explanation for choice of comparators {6b}

Our protocol consists of a lifestyle intervention (online training and dietary counseling) and a pharmacological intervention with metformin or placebo. We expect both interventions to postpone further pubertal progression by improving insulin sensitivity and/or by changing body composition in girls with overweight and early puberty. Since pharmacological suppression of puberty is not recommended for girls older than 8 years presenting with early puberty, the comparator will be placebo and no lifestyle intervention.

### Objectives {7}

Primary objective: To determine the effects of metformin treatment vs placebo during a 6-month period on bone age as a marker of pubertal maturation in girls with overweight and early puberty.

Secondary objectives:To determine the effects of metformin vs placebo and/or lifestyle intervention on bone age, breast development, height velocity, sex hormones, insulin sensitivity, metabolic markers, blood pressure, fitness level, daily physical activity level, and body composition*.*To determine the effects of metformin vs placebo and/or lifestyle intervention on quality of life (QoL).To determine the effects of metformin vs placebo and/or lifestyle intervention on age at menarche.

### Trial design {8}

The participants will be recruited from the DAnish Precocious Puberty study (DAPP study, Clinical Trial number NCT05957991) which is a nationwide longitudinal cohort study including children with early puberty to determine the incidence of central precocious puberty and to explore the impact of lifestyle and environmental factors on the timing of puberty. The DAPP study, which was initiated on December 1, 2023, will include all children referred for precocious puberty to each of the 17 pediatric departments in Denmark during a 3-year period.

LIFE-MET is a randomized, placebo-controlled, four-arm, multicenter trial with a 1:1 allocation ratio of a sub-cohort (*n* = 80) of participants from the DAPP study. The trial is a superiority trial comparing metformin to placebo. Allocation to metformin or placebo will be double-blinded. Eligible girls will be randomly assigned to one of the four trial arms: Metformin + lifestyle intervention (*N* = 20), Metformin alone (*N* = 20), Placebo + lifestyle intervention (*N* = 20), Placebo alone (*N* = 20). The intervention period is 6 months with follow-up after an additional 6 months.

## Methods: participants, interventions and outcomes

### Study setting {9}

The trial subjects will be recruited from five pediatric departments, each located in one of the five regions in Denmark: (1) Copenhagen University Hospital—Herlev (Capital Region), (2) Zealand University Hospital—Roskilde (Region Zealand), (3) Lillebaelt University Hospital—Kolding (Region of Southern Denmark), (4) Aarhus University Hospital (Central Denmark Region), (5) Aalborg University Hospital, Nord (North Denmark region). All trial centers provide an appropriate setting to examine participants and conduct study visits including the necessary equipment to perform the trial.

### Eligibility criteria {10}

Eligible participants are girls (*n* = 80), aged 8.0–9.5 years from the DAPP cohort with clinical and biochemical signs of early puberty and overweight.

#### Inclusion criteria

Age 8.0–9.5 yearsBreast development on clinical examination (≥Tanner B2)GnRH test with stimulated LH > 5 IU/l or non-stimulated LH > 0.3 IU/LOverweight defined by the International Obesity Task Force (IOTF) as BMI > 91 st centile (1.34 SDS) [51]Premenarcheal

#### Exclusion criteria

Known or suspected hypersensitivity or allergy to metforminDiabetes mellitusPrevious or active malignancyCardiac, pulmonary, hepatic, or renal diseases associated with significant decompensationPsychological problems likely to lead to significant non-compliance

### Interventions {11}

#### Interventions for each group {11a}

Participating girls will be randomly distributed into four subgroups (1:1):1a. Metformin + lifestyle intervention (*N* = 20)1b. Metformin alone (*N* = 20)2a. Placebo + lifestyle intervention (*N* = 20)2b. Placebo alone (*N* = 20)

##### Medication intervention

Metformin subgroups: Trial dose will be 1000 mg daily (1 scored tablet). Initiation dose will be 500 mg (½ tablet) for the first 14 days to avoid or mitigate adverse effects. The treatment period will last for 6 months in total (180 days).

Placebo subgroups: The placebo dose will be ½ tablet once daily for 14 days, and then 1 tablet once daily for the remaining period. The treatment period will last for 6 months in total (180 days).

The tablets containing the active substance (metformin) and those containing placebo will be indistinguishable from one another with the same shape, size, and color and will both have a score line.

##### Lifestyle intervention

The lifestyle intervention will consist of:

Nutritional counseling for the parents in groups is performed online by a trained physician:The nutritional counseling will consist of an online session after the baseline visit where parents will be informed about the latest recommendations of a healthy diet for children from the Danish Food Agency, including guidance for healthier grocery shopping. In addition, information leaflets developed by the Danish Food Agency will be handed out or send to the parents.

An online training program twice a week for 6 months supervised by training experts with a background in exercise physiology:2.The online training will consist of both aerobic exercises and strength training. Training sessions will take place online twice a week and will consist of circuit training and active virtual reality gaming (AVRG) using the application FitXR, MetaQuest3. The participants will be able to interact and exercise with a private group with their coach and peers in the application FitXR.

Circuit training is a workout that involves rotating through various exercises targeting different parts of the body, such as squats, burpees, and jumping jacks. It involves endurance training, high-intensity aerobics, and exercises performed in a circuit, similar to high-intensity interval training. Sessions will begin with a warm-up, followed by a 5–20-min circuit training which increases throughout the intervention period following a schedule, and ending with 15–20 min of AVRG using FitXR. The AVRG will primarily consist of dancing or boxing sessions, as these were judged to be the most suitable sports in FitXR for children in this age group during a feasibility trial.

Participants in the lifestyle intervention group will receive a fitness watch (Garmin Vivofit Junior 3) with the purpose of displaying daily steps taken and motivating the girls to increase their daily physical activity level.

Fitness level (aerobic performance and explosive strength) will be evaluated for all participants prior to and after cessation of the intervention period using the following validated tests adapted to children: standing long jump, a 20-m sprint, and the YYIR1C (Yo-Yo Intermittent Recovery Level 1 for Children) [52]. In addition, the participants should wear an activity tracker for 1 week prior to and after cessation of the intervention period.

#### Criteria for discontinuing or modifying allocated interventions {11b}

In case of gastrointestinal adverse effects of the medication, participants can be advised to divide the daily dose over two doses. In all participating girls, safety blood samples will be performed at baseline and at 3 and 6 months including renal (sodium (Na), potassium (K), creatinine, urea) and hepatic function tests (alanine transaminase (ALAT), bilirubin). A progressive increase of creatinine, urea, ALAT, or potassium levels will be a reason for discontinuing the medication. Persistent gastrointestinal adverse effects (vomiting, nausea, abdominal pain) and a persistent skin rash are also reasons for discontinuation of the medication.

Participants will be instructed to pause treatment with metformin or placebo in case of moderate or severe dehydration/repeated vomiting, severe infection requiring hospitalization, or in case of an operation requiring general, spinal, or epidural anesthesia. Participants will also be instructed to inform health personnel of their participation in the trial in case of hospitalization. In case of pausing treatment, participants are asked to inform the local PI.

#### Strategies to improve adherence to interventions protocols {11c}

Participants will be contacted by telephone after 1 month and will be seen every 3 months during the treatment period to maintain close contact and to monitor adherence and adverse events. In addition, participating girls and their families will be asked to fill out a short daily diary including adherence (tablets taken). Ultimately, adherence will be registered when participants return any unused medication after the intervention has ended (ratio between tablets dispensed and tablets returned by the patient at 6 months).

#### Relevant concomitant care permitted or prohibited during the trial {11d}

The participant can continue her concomitant therapy, except for any hormonal treatment including GnRH-agonists, sex hormones, or contraception.

### Provisions for post-trial care {30}

Not applicable. No such provisions have been made.

### Outcomes {12}

Primary outcome: Change in bone age from baseline to 12 months (difference in days).

Secondary outcomes:Breast development (puberty Z-scores [53])Anthropometry (height, weight, body mass index (BMI), waist-hip circumference, and ratio)Body composition (body fat percentage, lean mass, and gynoid/android fat distribution)Sex hormones (LH, FSH, estradiol, androgens, SHBG, AMH, and inhibin B)Insulin sensitivity (HOMA-IR) (calculated from fasting insulin and glucose)Age at menarche (electronic questionnaires)

Exploratory outcomes:Systolic blood pressure and resting heart rateMetabolic markers (i.e., cholesterol, triglyceride, leptin, and adiponectin)Fitness level (score)Daily physical activity level (time spent in different activity categories)Daily steps taken (only lifestyle intervention groups)Assessment of quality of life by online questionnaires (WHO-5 Well Being Score)

Safety parameters:Kidney and hepatic function tests (Na, K, urea, creatinine and ALAT, bilirubin)

Change in bone age after 12 months was chosen as the primary endpoint to evaluate the progression of puberty because both clinical and biochemical evaluations of pubertal stage can be challenging to accurately quantify. Automated determination of bone age will give us an objective measure of bone maturation which reflects growth velocity as an indicator of pubertal progression.

### Participant timeline {13}

Figure 1 outlines the diagram of the trial design. Figure 2 is a time schedule of enrollment, interventions, assessments, and visits for participants cf. the SPIRIT guideline (1).

**Fig. 1 Fig1:**
[figure not shown]
Diagram of the trial design

**Fig. 2 Fig2:**
[figure not shown]
Time schedule of enrollment, interventions, assessments and visits for participants. Cf. the SPIRIT 2013 guideline (1)

### Sample size {14}

Sample size was calculated using a study of girls with low birth weight who had early puberty and were treated with metformin. This treatment delayed pubertal progression, and age at menarche was 11.4 (SD 0.69) years in untreated girls and 12.5 (SD 0.44) years in metformin-treated girls (*P* < 0.0001) [38]. This difference is equal to 1 SD of age at menarche in Danish data. The former study used a lower dose of metformin, but the participants were treated for a longer period. Using a more conservative approach with a change of 0.5 SD in age at menarche (equivalent to delaying menarche from 11.4 (SD 0.69) years to 11.9 years), we found that with a significance level of 5% and power of 90%, there should be 80 girls (40 in each treatment group (metformin/placebo)) included to detect a difference. However, our primary outcome is change in bone maturation (change in bone age) as an earlier surrogate measurement of age at menarche because it describes pubertal progression. No other studies have explored the effect of metformin on pubertal progression determined by changes in bone age which hinders a sample size calculation based on the primary outcome. We therefore plan to include 80 girls (metformin (*n* = 40) or placebo (*n* = 40)). We will use an intention-to-treat approach, and data from all randomized subjects will be included in the statistical analysis.

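### The sample size labels the effect as 0.5 SD, but 80 girls and 90% power follow only from 0.72 SD, because two different SDs are mixed

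*Protocol article*

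**What the plan says.** Everything at issue is in the Protocol article, Sample size {14}. The starting point is an earlier study of girls with low birth weight and early puberty, where "age at menarche was 11.4 (SD 0.69) years in untreated girls and 12.5 (SD 0.44) years in metformin-treated girls". The section then places that difference on a national scale: "This difference is equal to 1 SD of age at menarche in Danish data". The Danish SD itself is not printed.

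The next step halves the effect and calls this more conservative; it works "with a change of 0.5 SD in age at menarche (equivalent to delaying menarche from 11.4 (SD 0.69) years to 11.9 years". The result is that "with a significance level of 5% and power of 90%, there should be 80 girls", split 40 and 40 between metformin and placebo.

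The section then says openly that the primary outcome is change in bone age, that no earlier study used this measure, "which hinders a sample size calculation based on the primary outcome", and that the figure of 80 is carried over. Outcomes {12} lists age at menarche as secondary. The planned number equals the calculated number, with no stated allowance for missing outcomes.

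**The concern.** An effect given as a fraction of an SD should be that fraction of the SD used in the power calculation. Here it is not. A shift of 0.5 years is half an SD only if the SD is about 1 year, yet the SD printed beside it is 0.69 years, against which the same shift is nearly three quarters of an SD.

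The label matters because standardised effects are what readers carry from one outcome to another. That is the step this section takes when it moves the number 80 from menarche to bone age. Someone who takes the label at face value will believe that 40 per group gives 90% power for a half-SD difference, and may then read a null result as excluding effects that the trial had little chance of detecting.

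**Working it through.** **Inputs, all from Sample size {14}.** Shift 11.9 - 11.4 = 0.5 years; SD 0.69 years; 40 per group; 5% significance; 90% power. The number of sides is not stated, so two-sided is assumed. The check is a plain two-group comparison of means with equal SDs.

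**Formulas.** With d = difference / SD:

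- n per group = 2 × (1.960 + 1.282)² / d² = 21.02 / d²
- power = Φ(d × √(n/2) - 1.960)

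The noncentral t distribution was used as a second check.

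**1. Reproduce the plan's figure.** d = 0.5 / 0.69 = 0.725. Then n = 21.02 / 0.525 = 40.0 per group. With 40 per group, d × √20 = 3.241, and Φ(3.241 - 1.960) = 90.0% (89.3% by t). So 80 girls and 90% follow from the printed years and the printed SD. A one-sided test would need only 33 per group, so two-sided is the reading that fits.

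**2. Take the label literally, d = 0.5.** n = 21.02 / 0.25 = 84.1, so 85 per group (86 by t). With 40 per group, 0.5 × √20 = 2.236, and Φ(0.276) = 60.9% (59.8% by t). A one-sided test gives only 72%.

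**3. Recover the Danish SD.** Two statements imply it:

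- 12.5 - 11.4 = 1.1 years is called 1 SD, so the SD is about 1.1.
- 0.5 years is called 0.5 SD, so the SD is about 1.0.

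If that spread applied to the trial's girls, then for a 0.5-year delay:

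| SD (years) | d | Power, 40 per group (normal / t) | n per group for 90% (normal) |
|---|---|---|---|
| 0.69 (printed) | 0.725 | 90.0% / 89.3% | 41 |
| 1.0 (implied) | 0.500 | 60.9% / 59.8% | 85 |
| 1.1 (implied) | 0.455 | 52.9% / 51.9% | 102 |

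The first row is 40.02 rounded up. No single SD gives both the half-SD label and 90% power with 40 per group.

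**4. Missing outcomes.** The documents give no rate, so 10% and 20% are assumptions. At d = 0.725, 36 per group gives 86-87% power and 32 per group gives 81-83% (t to normal).

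**5. Primary outcome.** The standardised difference detectable with 90% power depends only on the group size. With 40 per group and complete data it is √(21.02 / 40) = 0.725 by the normal formula, or 0.734 by t: about 0.73 SD. Turning this into days needs an SD for 12-month change in bone age, which the article does not give.

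**The case against.** The strongest reply is that the stated power is not wrong. The section prints its effect in years together with an SD, and from those two figures both 80 and 90% reproduce. That stands. The half-SD phrase comes directly after the sentence on Danish data, so it most naturally means half a Danish SD. A reader might infer that the calculation failed, or that the trial has only 60% power for the effect it targets. The article does not support either inference: it never states an effect of 0.5 on the SD used for power, and the 60% belongs to that different effect.

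Two further points stand. Assuming 0.5 years after an observed 1.1 years is cautious. So is using 0.69 in both groups: with the root-mean-square of 0.69 and 0.44, which is 0.579, power would be 97%. Nor is the Danish SD clearly the better choice, since the 0.69 comes from girls with early puberty, as in this trial, although they had low birth weight and were not selected for overweight.

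A reader might also think that sizing on a secondary outcome is concealed. It is not. Sample size {14} says so, and the Discussion concedes that the limited sample and duration could challenge power.

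Finally, these figures come from a two-group comparison, whereas Statistical methods {20a} plans mixed models. They describe the printed sample-size statement, not the exact power of the planned analysis.

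None of this repairs the label. The effect is scaled with one SD and powered with a smaller one, and the text does not say so.

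**Conclusion.** The point holds as a mismatch between the label and the calculation. The 90% belongs to a 0.5-year delay in menarche with an SD of 0.69, which is 0.72 SD, under a two-sided 5% test and with all 80 girls contributing. For a standardised effect of 0.5, 40 per group gives about 60% power, roughly 30 percentage points lower.

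The 52-60% for a 0.5-year delay is conditional on the Danish SD, which is only implied at 1.0 to 1.1 years, applying to these girls. The falls to about 86% and 81% are conditional on assumed missing rates of 10% and 20%, and are modest.

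For the primary outcome, the stated 90% says nothing directly. The lack of earlier studies prevents a calculation in days, but not a statement of the detectable difference in SD units, about 0.73 SD.

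**What to change.** Keep 80 girls and reword Sample size {14}:

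- Replace the half-SD label with: *a delay of 0.5 years, which is 0.72 SD when SD = 0.69*. The description of the assumption as conservative relative to the observed 1.1 years can stay.
- State that 40 per group gives about 89-90% power for this delay (two-sided 5%) with complete outcome data, about 86% or 81% under an assumed 10% or 20% missing, and about 60% for a true effect of 0.5 SD.
- If the Danish comparison is kept, print that SD and say why 0.69 was used for the power calculation.
- State that the 90% applies to age at menarche, a secondary outcome. Add that for 12-month change in bone age the difference detectable with 90% power, in a simple two-group comparison with complete data, is about 0.73 SD.

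The change is to wording only. No girls are added, and design and analysis are untouched. The cost is a less favourable stated power.
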